### 2.6. Dropout Criteria

Already enrolled participants will be dropped out if they withdraw their consent for participation, are lost to follow-up, cannot continue participation due to adverse events or complications, consume disallowed medications, or markedly deviate from the study protocol.

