### 2.12. Outcomes

#### 2.12.1. Primary Outcome

*Dizziness Handicap Inventory (DHI)*. DHI was developed to evaluate functional, emotional, and physical impairments due to dizziness [26]. This widely used scale for patients with dizziness is a patient-rated outcome (PRO) and has been validated in Korean [27]. The scale consists of 25 items (0, 2, or 4 scores/item, 0–100 scores). The primary endpoint is the mean difference of DHI total score between the baseline and the endpoint of the treatment period. Secondarily, the before-and-after effect of GJD between the baseline and every visit will also be investigated.

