#### 2.12.5. Cost-Effectiveness Assessment

The EuroQoL five dimensions' questionnaire (EQ-5D), consisting of two parts, that is, EQ-5D-5L and EQ VAS, will be used to assess quality of life, based on which QALY will be calculated. The Korean version of EQ-5D scale has been studied on its validity and reliability [57]. Also, direct costs (medical and nonmedical expenses) incurred in treating dizziness during the treatment (8 weeks) and follow-up (up to 12 months from randomization) periods will be investigated (Table 1). Medical fee signifies the cost paid in hospitals or clinics. Nonmedical fee signifies transportation and time costs that patients would incur for dizziness treatment. Based on the calculated QALY and fees, the incremental cost-effectiveness ratio (ICER) will be estimated (ICER = Δ  cost/Δ effectiveness). The ICER signifies the amount of cost necessary to improve by 1 unit of effectiveness.

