### 2.13. Sample Size Calculation

To calculate the effect size, we used a preceding RCT on acupuncture therapy for MD with DHI assessment, as there have been no clinical studies for GJD effectiveness in chronic dizziness [58]. The null hypothesis is that *μ*_GJD_ = *μ*_placebo_, while the alternative hypothesis is *μ*_GJD_ ≠ *μ*_placebo_, where *μ* denotes the mean difference of DHI score between the baseline and endpoint. With the mean difference (−3.63) and the standard deviation (4.84), under the assumption of correlation coefficient (0.1), the sample size was calculated as 29 per group (two-sided, *α* = 0.05 and 1 − *β* = 0.8). Therefore, we are going to recruit 78 participants for both groups (39 per group) under a 25% anticipated dropout rate.

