### 2.14. Statistical Analysis

The primary and secondary variables for the effect assessments will be statistically analyzed by analysis of covariance (ANCOVA) or rank ANCOVA with group and site as covariates. If any demographic characteristics show significant difference between groups, those variables will also be used as covariates. When there is a significant interaction between diagnosis (MD, psychogenic dizziness, or dizziness of unknown cause) and group, subgroup analysis will be performed.

The confidence interval (CI) of BI will be addressed and blinding will be deemed successful when the CI includes the zero value. For safety assessment, the chi-squared test or Fisher's exact test will be performed with the proportions of AEs, while lab results will be compared between groups by chi-squared test (proportions of abnormal results) or McNemar's test (before-and-after comparison within a group). An independent statistician ([name]) will analyze any data with a significance level of 0.05 (two-sided) with SAS 9.4 software (SAS Institute Inc.).

The primary analysis will be performed with the full analysis set, which is defined as the group of participants who were prescribed at least once or more the GJD or placebo pills and for whom DHI was evaluated more than once. The missing data will be imputed with the last observation carried forward method. The per protocol set will be additionally analyzed, which includes only the participants who complete all the scheduled visits. We are going to include any participants who took at least one pill of the study drugs for the safety assessment.

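### Last observation carried forward is the only missing-data method for the primary DHI analysis with 25% dropout expected; it can bias the week-8 contrast, and its reach to EQ-5D and costs is left open

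*Protocol article*

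**What the plan says.** Section 2.14 makes the full analysis set primary and then gives one rule: "The missing data will be imputed with the last observation carried forward method". The sentence is not limited to any outcome, and no missing-data sensitivity analysis is named. The full analysis set requires study medication to have been prescribed at least once "and for whom DHI was evaluated more than once". The second effect analysis is the per-protocol set, "which includes only the participants who complete all the scheduled visits".

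Section 2.13 sets 39 per group "under a 25% anticipated dropout rate". Section 2.6 lists among the reasons for dropout that participants "cannot continue participation due to adverse events or complications, consume disallowed medications, or markedly deviate from the study protocol".

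Table 1 schedules DHI at V1 and V2 (both before treatment) and at V3, V4, V5 and V6 (days 14, 28, 42 and 56). EQ-5D is scheduled at day 0, day 28, day 56 and months 4, 8 and 12. Section 2.12.5 on cost-effectiveness gives no missing-data rule of its own.

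**The concern.** LOCF enters an early score as if it were the observed week-8 score. When DHI changes over the eight weeks, the estimate then mixes the treatment effect with how many people left and when, and no uncertainty is added for the filled-in values. With 25% dropout this touches about 10 of 39 participants per arm (0.25 × 39 = 9.75).

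Three features sharpen the point:

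- Adverse events and disallowed medication are among the dropout reasons, so dropout may depend on arm or on symptoms.
- A participant with DHI at V1 and V2 only has been evaluated more than once and so meets the DHI condition of the full analysis set. LOCF would give that person a change of zero.
- The per-protocol analysis does not repair this. A completers-only set has its own selection problem and is not a missing-data sensitivity analysis.

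At stake are the size of the primary estimate, its power and, under unequal dropout, its error rate.

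**Working it through.** **The plan's own figure.** Inputs from section 2.13: difference 3.63, SD 4.84, two-sided α 0.05, power 0.80.

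- Standardised difference: 3.63 / 4.84 = 0.75.
- Normal approximation: n = 2 × (1.96 + 0.842)² / 0.75² ≈ 27.9, so 28. The t-test solution is 28.9, so 29 per group.
- Dropout: 29 / 0.75 = 38.7, so 39 per group.

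Both stated figures reproduce. Reading 4.84 as a single-visit SD with correlation 0.1 gives an SD of change of 4.84 × √1.8 = 6.49 and n = 51, which does not match. So 4.84 acts as the SD of change.

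**Assumptions, since the documents give no dropout timing, dropout split or placebo change.** The mean DHI change is linear over 56 days. The last DHI of a dropout is spread evenly either over V3–V5 or, allowing baseline to be carried, over V2–V5. The average share of the eight-week change not yet seen is then

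- V3–V5: (0.75 + 0.50 + 0.25) / 3 = 0.5
- V2–V5: (1 + 0.75 + 0.50 + 0.25) / 4 = 0.625

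**Equal dropout of 25%, planned effect true.** Expected LOCF estimate = 3.63 × (1 − 0.25 × share).

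- V3–V5: 3.63 × 0.875 = 3.18 (−12.5%)
- V2–V5: 3.63 × 0.844 = 3.06 (−15.6%)

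**Equal dropout, no drug effect.** The bias is zero. Simulated rejection is about 5% at every level of shared improvement tried.

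**Unequal dropout, no drug effect.** Bias = (difference in dropout) × share × (shared improvement). It works against the arm with more dropout. For 15% versus 35%:

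| Shared improvement | Share 0.5 | Share 0.625 |
|---|---|---|
| 5 points | 0.2 × 0.5 × 5 = 0.50 | 0.2 × 0.625 × 5 = 0.63 |
| 10 points | 0.2 × 0.5 × 10 = 1.00 | 0.2 × 0.625 × 10 = 1.25 |

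Simulation with 39 per arm, SD of change 4.84 and correlation 0.1 gives type I error of about 7–16% for a change-score comparison and about 9–21% with baseline adjustment. Adjusting for baseline therefore does not cure the problem.

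**Direction when the planned effect is true** (10 points of shared improvement, share 0.5):

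- 35% dropout on GJD, 15% on placebo: −13.63 × 0.825 + 10 × 0.925 = −2.0
- 15% on GJD, 35% on placebo: −13.63 × 0.925 + 10 × 0.825 = −4.4

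The truth is −3.63 in both cases.

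**Power, like for like** (25% dropout in both arms, both methods baseline-adjusted, baseline may be carried). A repeated-measures model has about 96%. LOCF has about 95%, 88% and 74% for shared improvement of 0, 5 and 10 points. The loss is about 0, 8 and 22 percentage points, and smaller if every dropout has a post-baseline DHI.

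**If LOCF were applied to EQ-5D.** Share of the 12-month QALY period after the last observation:

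- last seen at V6: (365 − 56) / 365 = 85%
- after month 4: 8 / 12 = 67%
- after month 8: 4 / 12 = 33%

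**The case against.** The strongest reply is that the harm is conditional. With equal dropout and no drug effect, LOCF is unbiased and holds 5%. With equal dropout and a real effect, the bias is toward the null. Inflation needs dropout, or its timing, to differ by arm together with change over time, and the documents state neither. A milder 28% versus 22% split gives only about 5–6% type I error. All of this stands, so a reader should not infer that LOCF necessarily biases the contrast or breaks the error rate.

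A second tempting inference is that a repeated-measures model would lift power from 60–80% to 96%. That sets an unadjusted change score against a baseline-adjusted model. An unadjusted change score with no missing data at all reaches only about 90%, so much of the gap comes from baseline adjustment. Only the like-for-like losses above belong to LOCF.

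A third is that LOCF supplies most of the 12-month QALY for dropouts. The sentence does not name EQ-5D or costs, and it stands in the paragraph that defines a DHI-based set. A condensed article may leave the economic rule to the full protocol or analysis plan. Even if LOCF applied, most of the period would not be imputed for someone last seen at month 8.

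Finally, the simulated dropout did not depend on outcome, which suits a repeated-measures model. Under such dropout a completers analysis also holds 5%. This is why the model needs a sensitivity analysis beside it.

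The reply does not remove the core. LOCF is a stated rule for the primary analysis, not a detail left for later, and a quarter of participants are expected to leave.

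**Conclusion.** The concern holds in conditional form. LOCF is a poor choice as the sole method for the primary DHI analysis at 25% dropout.

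- With equal dropout and a linearly building effect, it shrinks 3.63 to about 3.1–3.2 points and leaves type I error near 5%.
- With unequal dropout and improvement in both arms, it can bias the contrast either way. At 15% versus 35% and 5 to 10 points of shared improvement, the null bias is about 0.5–1.25 points and type I error about 7–21%.
- The like-for-like power loss runs from about 0 to 22 percentage points.

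The 25%, 3.63, 4.84 and 0.1 are the plan's figures. The linear course, the timing and split of dropout and the shared improvement are assumptions. For EQ-5D and costs, the supportable statement is only that the unrestricted wording leaves the scope of LOCF open.

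**What to change.** Make the primary analysis a mixed model for repeated measures on DHI at V3–V6, with group by visit, baseline DHI by visit and site, and take the week-8 group contrast as primary. Add a reference-based or delta-adjusted sensitivity analysis. Keep LOCF, if wanted, as a further sensitivity analysis only.

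Restrict the LOCF sentence so that it does not cover EQ-5D and costs at months 4 to 12, and specify multiple imputation there.

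No new data are needed, because Table 1 already collects DHI at every one of these visits. The cost is revised wording and modest programming, best done before unblinding. The downside is reliance on missing at random, which the sensitivity analysis is there to probe. The secondary before-and-after DHI analysis in section 2.12.1 is a separate matter and need not change for this point.

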### 2.2. Study Design

This study will be a prospective, multicenter, randomized, double-blind, placebo-controlled, parallel-group, clinical trial. Seventy-eight patients diagnosed with MD, psychogenic dizziness, or dizziness of unknown cause, with a DHI score ≥ 24 at baseline, and having complained of dizziness for more than 1 month will be randomized and allocated to either the GJD or placebo group in a 1 : 1 ratio. They will be orally given 3.75 g GJD or placebo in pill form once a day for 8 weeks (56 pills in total). To collect data for the cost-effectiveness analysis, we will follow up the patients for up to 12 months from randomization. The study flowchart is displayed in diagram form in Figure 1 and the specified timetable is presented in Table 1.

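### The per-protocol set depends on attending the 4-, 8- and 12-month cost visits, which fall after the week-8 DHI endpoint has closed

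*Protocol article*

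**What the plan says.** Section 2.14 gives the per-protocol rule in one sentence: "The per protocol set will be additionally analyzed, which includes only the participants who complete all the scheduled visits". It sets no limit on which visits count.

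Section 2.2 explains the late visits: "To collect data for the cost-effectiveness analysis, we will follow up the patients for up to 12 months from randomization". In Table 1 these are V7, V8 and V9, and the only rows marked there are EQ-5D and cost information. DHI is marked at V1 to V6 only.

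Section 2.12.1 fixes the outcome: "The primary endpoint is the mean difference of DHI total score between the baseline and the endpoint of the treatment period". In Table 1 the treatment period ends at V6, day 56.

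The primary analysis uses the full analysis set. Section 2.14 describes it by two conditions. The first concerns treatment: "the group of participants who were prescribed at least once or more the GJD or placebo pills". The second concerns the outcome and admits those "for whom DHI was evaluated more than once". On missing values the section says: "The missing data will be imputed with the last observation carried forward method".

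**The concern.** A per-protocol analysis should ask what happened to participants who followed the plan up to the point where the outcome was measured. Here membership is decided up to ten months after that point. Someone who complied fully and gave every DHI score to week 8 is removed for missing the month-12 cost visit.

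Attendance after the outcome may depend on how the participant fared, or on the arm. If it does, the rule selects on a consequence of the result, and the per-protocol comparison can be biased in either direction. If it does not, the rule only discards usable data. In both cases a difference between the per-protocol and primary results could no longer be read as an effect of protocol adherence.

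The full analysis set raises a lesser question. A condition of more than one DHI looks intended to secure a score under treatment, but the schedule lets two pre-treatment scores satisfy it.

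**Working it through.** **1. The plan's own sample size.** Inputs from section 2.13: difference 3.63, SD 4.84, two-sided alpha 0.05, power 0.80, dropout 25%.

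- Normal approximation: n = 2 × [4.84 × (1.960 + 0.842) / 3.63]² = 27.9, so 28 per group.
- Two-sample t-test (noncentral t): 28.9, so 29 per group, as stated.
- Dropout: 29 / 0.75 = 38.7, so 39 per group and 78 in total, as stated.

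Neither set definition enters this calculation.

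**2. Visits against outcomes (Table 1).**

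| Visits | Time | DHI | EQ-5D or cost |
|---|---|---|---|
| V1, V2 | screening, day 0 | both | EQ-5D at V2 |
| V3 to V6 | days 14 to 56 | all | cost at all, EQ-5D at V4 and V6 |
| V7 to V9 | 4, 8, 12 months | none | both, at all three |

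Three of the nine scheduled visits contribute nothing to the DHI outcome, yet all three are conditions for entering the per-protocol set.

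**3. How many could be lost.** Section 2.13 does not say which time point the 25% refers to, so two cases frame the range.

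- *The 25% covers all 12 months.* About 78 × 0.75 = 58.5 complete every visit, so the set is no smaller than planned. Some of the other 19.5 may still have a week-8 DHI; the documents do not say how many.
- *The 25% is all lost by week 8.* Then 58.5 reach V6. Assume that a share f of them misses at least one of V7 to V9:

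| f (assumed) | Discarded, 58.5 × f | Left, 58.5 × (1 − f) | Per group | Standard error, 1/√(1 − f) | t-test power for 3.63, SD 4.84 |
|---|---|---|---|---|---|
| 0 | 0 | 58.5 | 29.25 | 1.00 | about 80% |
| 10% | 5.9 | 52.7 | 26.3 | 1.05 | about 76% |
| 20% | 11.7 | 46.8 | 23.4 | 1.12 | about 71% |
| 30% | 17.6 | 41.0 | 20.5 | 1.20 | about 65% |

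The table shows lost precision only. The documents give no figure from which the bias could be sized.

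**4. The full analysis set.** Two DHI scores, at V1 and V2, exist before any treatment effect is possible. A participant followed as scheduled to day 0 already meets the condition, so it excludes almost no one. If that participant gives no later DHI, last observation carried forward enters the V2 score at week 8. The change is zero if V2 is baseline; if V1 is baseline, it is the V1-to-V2 difference.

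Which score is baseline is not named. Section 2.2 requires "DHI score ≥ 24 at baseline", and Table 1 marks the eligibility assessment at V1 only. The other efficacy scales that have a baseline value start at V2.

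As an illustration, take V2 as baseline, 39 per group, SD held at 4.84, and the same assumed share p in each arm with only V1 and V2 scores. The expected difference is 3.63 × (1 − p). For p = 5%, 10% and 25% this is 3.45, 3.27 and 2.72. Normal-approximation power is 88%, 85% and 70%, against 91% at p = 0.

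**The case against.** **The sponsor may have meant treatment visits only.** That is plausible, but section 2.14 says all scheduled visits, and section 2.2 and Table 1 make V7 to V9 scheduled visits. The text needs the limit stated.

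**The per-protocol analysis is only additional.** This stands. The defect in the per-protocol rule does not touch the primary analysis, which uses the full analysis set.

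**The loss at V7 to V9 is assumed.** This also stands. The 10% to 30% range comes from no figure in the documents, and the case of no loss beyond plan belongs in it.

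**A reader might infer that the per-protocol set ignores adherence.** The documents do not support that. Under section 2.6, participants who take disallowed medication or deviate markedly are dropped, so they would not complete the visits. A pill-intake threshold may sit in the full protocol, which is not shown, and its absence from an article is no fault.

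**A reader might infer that the full analysis set is also wrongly defined.** This goes too far. A set that keeps nearly every randomised participant is close to intention to treat. The use of a pre-treatment score as the week-8 outcome comes from last observation carried forward. Redefining the set as all randomised would not remove it without changing the analysis method, and section 2.14 names only ANCOVA or rank ANCOVA.

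**Conclusion.** The concern holds for the per-protocol set. As worded, it makes inclusion depend on attendance at three visits that carry no DHI and follow the primary endpoint. Participants with valid week-8 results can be excluded, at a cost in precision and with a risk of selection bias. The size ranges from no loss beyond the planned 25%, if that figure covers 12 months, to about 6 to 18 of some 58 week-8 completers. The latter assumes that the 25% is all lost by week 8 and that 10% to 30% of completers then miss a later visit. Only a supportive analysis is affected.

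On the full analysis set the conclusion is narrower. Its DHI condition does almost nothing as worded, and together with the carry-forward rule it admits pre-treatment scores as week-8 outcomes. That calls for clarification and is not an error in the set itself.

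**What to change.** Make the changes in section 2.14, or in the analysis plan, before unblinding:

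- **Per-protocol set:** define it on visits through V6, with the week-8 DHI obtained and no disallowed treatment or marked deviation (the criteria already in section 2.6) up to V6. Make no reference to V7 to V9. If the economic analysis needs a set of 12-month completers, define that separately.
- **Full analysis set:** say whether the DHI condition means at least one score after the first dose. If it does, write that. If the aim is to keep nearly all randomised participants, drop the condition and acknowledge that the carry-forward rule will enter pre-treatment scores for those with no later DHI.
- **Baseline:** name the V2 score as the DHI baseline.

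These are wording changes. They need no new data, visits or participants, and 29, 39 and 78 stay as they are. Replacing last observation carried forward would be a change of method and a separate decision.

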## 3. Results and Discussion

This study is a prospective, multicenter, randomized, double-blind, placebo-controlled, parallel-group, clinical trial to explore the effectiveness, safety, and cost-effectiveness of a herbal drug, GJD, for patients with chronic dizziness attributable to MD, psychogenic dizziness, or dizziness of unknown cause. We are going to administer to patients GJD or placebo pills for 8 weeks and follow them up for 12 months. Four TKM hospitals in Korea will enroll 78 participants.

Dizziness may ensue from a variety of central or peripheral diseases and in some cases as a drug complication. This may complicate the diagnostic process. This study will include patients diagnosed with MD, psychogenic dizziness, or dizziness of unknown cause, which may create an issue with homogeneity. However, there were previous clinical studies which also focused on the symptom of dizziness with varied origin to demonstrate new efficacy [28, 35], including an acupuncture study for chronic dizziness [24], which has meaningfully been referred for this trial.

GJD is a widely prescribed herbal pill in Korea, but it is mostly used for patients with severe deficiency pattern/syndrome, especially those complaining of marked fatigue [14, 21]. However, based on the seminal work* Dongeuibogam* [10], we expect GJD to also manage chronic dizziness.

This RCT included various diseases (MD, psychogenic dizziness, or dizziness of unknown cause) inducing dizziness, which might reduce the level of homogeneity of patient population. The investigators discussed this issue, which might affect significantly the study results in the future. However, it was taken into consideration that this trial should reflex the real clinical practices as much as possible, which means that GJD is a herbal drug and it has been described based on pattern/syndrome identification in TKM. So, we think the screening process is one of the key parts for this trial to include eligible participants. Investigators and coordinators should be trained with written standard operating procedures for the trial before enrolling the first participants, since this study is a multicenter trial, to control the high quality throughout the whole process. Also, an independent monitor will regularly visit all the hospitals for auditing ethical and scientific issues.

## 4. Conclusions

We are going to conduct a prospective, multicenter, randomized, double-blind, placebo-controlled, parallel-group, clinical trial on patients with chronic dizziness to evaluate the effectiveness, safety, and cost-effectiveness of a herbal drug, GJD. This study has been approved by an ethics committee and registered in the WHO international clinical trials registry platform (CRIS), in the Republic of Korea.

